### Knowledge of depression

A 12-item questionnaire was designed to measure knowledge of depression. This questionnaire will be used to add credibility to the control intervention and as a proxy measure for whether the control emails are read. It will be administered at baseline and at post intervention. Each question relates to the content of one control Mood Memos email. The response scale is *true*, *false*, *don't know*, with one point for each correct answer, giving a range of scores from 0 to 12. The questionnaire was piloted on the working group, and six members of the public.

### Self-efficacy

Participants will be asked "How confident are you in your ability to help yourself improve your depression symptoms?" at baseline and at post intervention. The response scale used is *not at all confident*, *a little confident*, *moderately confident*, *very confident*, *don't know*. Self-efficacy was measured as an intermediary effect because it is a predictor of behaviour change [30] and short-term health promotion campaigns often only demonstrate improvement in intermediary effects rather than behaviour change.

### Other

Characteristics of participants including age, gender, personal history of depression or psychotic disorders, education level, and ethnic background will be assessed at baseline. These are collected as potential predictors of intervention response. Participants will also be asked at each assessment point whether they had sought help from a health professional recently for their depression symptoms, to eliminate this as a confounding variable. Qualitative data on participants' experience of the study will be collected via a feedback form at the post-intervention assessment.

### Statistical analysis

Primary effectiveness analyses will be undertaken on an intention-to-treat basis. Any participants who were randomised but who withdraw from the study, or who take up alternative treatments, will be included in the analysis as randomised. Continuous outcomes (PHQ-9 scores, K10 scores, WSAS scores) will be evaluated using mixed models for repeated measures (MMRM) [68]. This method of analysis will be utilised because of its ability to include participants with missing data under the assumption that observations are missing at random (MAR). The inclusion of an additional measurement occasion halfway through the intervention should increase the tenability of the MAR assumption. *A priori *contrasts will compare change from baseline at the primary endpoint (post-intervention) and at 6-months follow up. Dichotomous outcomes will be defined. These include the development of probable major depression (as indicated by PHQ-9 results) in participants who did not meet this criterion at baseline and remission from sub-threshold depression in those who fell into this category at baseline. Relative risk will be calculated and tested for significance. The numbers needed to treat to avoid one person developing major depression and to achieve one remission from sub-threshold depression will be calculated.

In addition to intervention group, a number of variables will be examined to see if they predict outcomes: age, gender, education level, past diagnosis of depression, past diagnosis of psychotic disorder, whether they sought help during the intervention, baseline self-help for depression self-efficacy, and whether they had experienced an adverse life event in the six months prior to the development of sub-threshold depression.

Other outcomes include coping strategies used, knowledge of depression, and self-help for depression self-efficacy. In order to determine whether any change in depression might be due to changes in coping behaviour, the coping strategies used by participants will be evaluated. Usage rates and change in usage of each strategy in each intervention group will be compared pre- and post-intervention. Change in use of each strategy will be evaluated using logistic regression expressed as odds ratios with their 95% confidence intervals. Each strategy's mean perceived helpfulness for participants using them will also be compared pre- and post-intervention between groups.

Assessment attrition will be described at each assessment point. Participant characteristics and levels of depression will be analysed as predictors of missingness within each group. Email usage adherence will be explored by comparing frequencies of email image downloads between groups. Possible multiple enrolments will be explored by examining small variations and patterns in participant names, IP addresses and email addresses [69].

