### Sample size

The effect size of the intervention is anticipated to be small, given that indicated prevention of depression has a small effect size of d = 0.23 [18]. Similarly, unsupported internet-based treatment of depression has a small effect size of d = 0.25 [14]. A power analysis indicated that a sample of 393 per condition would give 80% power to detect a small effect size (0.2 standard deviations between conditions) on a continuous outcome measure assuming a correlation of 0.5 between pre- and post-test scores [19]. Because depression internet trials have a median dropout rate of 33% [20], a total sample of 1200 participants will be aimed for.

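### Missing data are handled for the continuous scores only; for major depression and remission the plan states just a relative risk, which does not by itself deliver the promised intention-to-treat inclusion

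*Protocol article*

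**What the plan says.** The first paragraph of Statistical analysis in the protocol article opens with "Primary effectiveness analyses will be undertaken on an intention-to-treat basis" and continues: "Any participants who were randomised but who withdraw from the study, or who take up alternative treatments, will be included in the analysis as randomised". It then assigns mixed models for repeated measures (MMRM) to the continuous outcomes, listed as PHQ-9, K10 and WSAS scores, and gives the reason: "This method of analysis will be utilised because of its ability to include participants with missing data" under MAR. The mid-intervention assessment is said to make that assumption more tenable. The planned contrasts are at the end of the intervention (the primary endpoint) and at 6 months.

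The dichotomous outcomes follow. "These include the development of probable major depression (as indicated by PHQ-9 results) in participants who did not meet this criterion at baseline", together with remission from sub-threshold depression. Their analysis is "Relative risk will be calculated and tested for significance", plus a number needed to treat for each. No covariate, time point or approach to missing PHQ-9 data is attached to them.

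Three other places matter:
- The Abstract puts prevention of major depression into the primary hypothesis, beside symptom reduction.
- The Assessment section derives the probable diagnoses from the same PHQ-9 that gives the severity score.
- The Sample size section sets the total at 1200: "Because depression internet trials have a median dropout rate of 33"%.

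**The concern.** One questionnaire, with one set of missed assessments, is treated in two ways. The severity score gets a likelihood-based method that uses every available PHQ-9. The diagnosis derived from that PHQ-9 gets an effect measure that needs a known status for each person and does not say where the status comes from when the questionnaire is missing. Unless something is added, status must come from completers alone or from a fixed rule such as counting the missing as non-cases. The first does not include withdrawn participants as randomised. The second rests on an assumption different from the MAR assumption adopted for the score.

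The prevention half of the primary hypothesis, and both numbers needed to treat, rest on these outcomes. If dropout depends on the 3-week PHQ-9 and does so differently in the two arms, the severity analysis can allow for it and the relative risk from observed status cannot. The two results could then disagree because of how missing data were treated, not because of the emails.

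**Working it through.** **1. The plan's own figures.** Inputs from Sample size: difference 0.2 SD, power 80%, pre-post correlation 0.5, dropout 33%. Two-sided alpha of 0.05 is assumed, since none is stated.
- SD of change = sqrt(2 × (1 − 0.5)) = 1.
- n per arm = 2 × (1.960 + 0.842)² / 0.2² = 392.4, so 393. The stated figure is reproduced.
- Total with dropout = 786 / 0.67 = 1173.1, so 1174. The target of 1200 is consistent with this.

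**2. How many people are at issue.** At 33% dropout, 0.33 × 1200 = 396 would have no observed status and 804 would (402 per arm with equal allocation).

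**3. Bias under the plan's own MAR assumption.** The documents give no event rates and no dropout by arm, so all rates here are assumed.
- In each arm half score high on the 3-week PHQ-9, with later risk 25%, and half score low, with later risk 5%.
- True risk in both arms = 0.5 × 0.25 + 0.5 × 0.05 = 15%, so the true relative risk is 1.00.
- Active dropout is 33% throughout. Control dropout is 46% if high and 20% if low, on average 0.5 × 0.46 + 0.5 × 0.20 = 33%.
- Dropout depends only on arm and the 3-week score, which is taken as observed in everyone. This is MAR.

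Controls:
- Observed fraction = 0.5 × 0.54 + 0.5 × 0.80 = 0.67.
- Observed cases = 0.27 × 0.25 + 0.40 × 0.05 = 0.0875.
- Completer risk = 0.0875 / 0.67 = 13.1%.

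Active: completer risk = 15.0%.

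| Approach | Relative risk (truth 1.00) |
|---|---|
| Completers | 0.150 / 0.1306 = 1.15 |
| Missing counted as non-cases | 0.1005 / 0.0875 = 1.15 |
| Missing counted as cases | 0.4305 / 0.4175 = 1.03 |
| Standardised over 3-week score within arm | 0.15 / 0.15 = 1.00 |

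Here 0.1005 = 0.67 × 0.15, and the third row adds 0.33 to each arm. Exchanging the arms gives a completer relative risk of 0.1306 / 0.150 = 0.87. The risk difference is then 0.0194, which would be reported as a number needed to treat of about 1 / 0.0194 = 52 for an intervention with no effect.

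**4. Precision.** Power of a two-sided 5% test of two proportions, again with assumed rates:

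| Risks | 402 per arm | 600 per arm |
|---|---|---|
| 10% vs 7% | 33% | 46% |
| 15% vs 10% | 57% | 75% |
| 20% vs 15% | 46% | 63% |
| Remission 40% vs 50% | 81% | 94% |

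The gap is 12 to 17 percentage points. The right-hand column is an upper bound, because imputation recovers only part of the lost information.

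**The case against.** The strongest reply is that a relative risk is an effect measure, not a missing-data method. It can be computed after imputation or from a longitudinal binary model, and the same paragraph says that withdrawn participants are included. A reader might infer that the plan drops about a third of its participants. The article does not say so: it never specifies complete cases, 33% is a median from other trials, and the time point for developing major depression is open. The Trial procedure section also lets people rejoin at later assessments. This stands, and the loss of 396 is therefore conditional. Rejoining helps only in part, since the PHQ-9 covers the last two weeks and a later form cannot show an episode at a missed assessment.

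A second reply is that a condensed article may leave missing-data detail to the full protocol or analysis plan. For silence alone that would settle the matter. But this article does state an assumption, a method and the reason for it, limits the method to the continuous scores, and names a different analysis for the binary outcomes.

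A third reply is that completer risks are not always biased. They are unbiased if dropout within arm is unrelated to outcome, and a correctly specified baseline-adjusted completer model is valid if dropout depends only on baseline variables. That is right. The section also plans to study predictors of missingness within each group, though not to use them in the relative risk.

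A larger bias is easy to construct. Suppose that true risk is 15% in both arms, active dropout is unrelated to outcome, and controls drop out at 50% with major depression and 30% without it. The completer relative risk is then 0.15 / (0.075 / 0.670) = 1.34. That example should not be used against the plan without a label. Dropout there depends on the outcome itself, so the data are missing not at random (MNAR). Standardising over a fully observed 3-week score, with an assumed 3-to-6-week correlation of 0.5, 0.6 or 0.7, still gives 1.30, 1.27 or 1.24. The MAR remedy would correct it only in part.

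**Conclusion.** The concern holds in a conditional form. The means of keeping withdrawn participants in the analysis is given for the continuous scores and not for the binary outcomes, which carry half of the primary hypothesis. As stated, the relative risk makes no use of the 3-week or screening PHQ-9 and does not by itself meet the intention-to-treat commitment. The reach of that commitment is itself implied: it refers to primary effectiveness analyses, and the Abstract's primary hypothesis brings major depression within them.

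If status is taken as observed, about 396 of 1200 are left out at the planning dropout. A relative risk of 1.15 or 0.87 can then arise with no true effect under MAR. The size and direction rest on assumed event rates and arm-specific dropout. The documents give no reason to expect one direction, and the figures are illustrations, not forecasts. This is a change that should be made; it does not undermine the severity analysis.

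**What to change.** Amend the Statistical analysis section for the two dichotomous outcomes as follows.

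1. Name the time point: post-intervention, with 6 months as the second contrast, matching the contrasts already set for the scores.
2. Estimate the relative risk and number needed to treat for all randomised participants under the same MAR assumption as the MMRM. Multiply impute the PHQ-9 items and the functional-impact item, separately by arm, from all PHQ-9 occasions (screening, 3 weeks, 6 weeks, 6 months) plus any predictors of missingness that the planned attrition analysis finds. Derive status from the imputed items, because the diagnosis depends on the symptom count and impact and not on the total score alone.
3. Fit a log-binomial or modified Poisson model adjusted for the screening PHQ-9, and pool over imputations.
4. Report as sensitivity analyses the complete-case result and at least two MNAR results, for example missing counted as events and a delta-adjusted imputation.

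The cost is some extra analysis work. No new data are needed, since every input is already collected under Table 2.

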## Abstract

**Background:**

Sub-threshold depression is common, impairs functioning, and increases the risk of developing major depression. Although psychological treatments have been investigated for sub-threshold depression, they are costly. A less costly alternative could be an educational health promotion campaign about effective self-help for depression symptoms. The aim of the study is to test the efficacy of a low-cost email-based mental health promotion campaign in changing self-help behaviour and preventing more severe depression in adults with sub-threshold depression.

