### Aim

The aim of the study is to determine the effectiveness of a mental health promotion campaign encouraging the use of a range of self-help coping strategies for sub-threshold depression, which have been identified by experts in the field. The study will evaluate the feasibility of the internet as a means of intervention, and will evaluate the impact of the intervention on depression symptom severity and incidence rates of major depression.

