### Assessment

Assessment is conducted at baseline (immediately prior to receiving the first Mood Memos email), midway through the intervention (3 weeks post-baseline), at the end of the intervention (6 weeks post-baseline), and 6 months after the end of the intervention (see Table 2 for outcome measures and time points of assessment). All assessment is based on self-report and is completed on the project website. The assessment is aimed to take little time to complete in order to discourage dropout attrition [41] whilst providing critical data. Time to complete questionnaires is estimated to range from 2 minutes (mid-intervention and 6-month follow-up assessment) to 6 minutes (for baseline and post-intervention assessment). The primary outcome is depression symptom severity (assessed with the PHQ-9 [42]). This outcome will also be categorised to yield probable depression diagnoses. Secondary outcomes are psychological distress (assessed with the K10 [43]) and level of functioning (assessed with the Work and Social Adjustment Scale [44]).

**Table 2 T2:** Outcome measures and timepoints of assessment

Assessment	Screening	Baseline	Mid-intervention	Post-intervention	6 months follow up
List of Threatening Experiences		X			

Sociodemographics		X			

PHQ-9	X		X	X	X

K10		X	X	X	X

Work and Social Adjustment Scale		X	X	X	X

Self-efficacy		X		X	

Knowledge of depression		X		X	

Coping questionnaire		X		X	

Help-seeking question			X	X	X

Qualitative feedback				X	

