### Coping questionnaire

Participants are asked to rate the frequency and perceived helpfulness of 26 coping strategies for depression symptoms over the past month at baseline and at post intervention. The coping strategies include the 14 used in the Mood Memos emails, as well as other strategies that were rated in the expert study [10] as relatively unhelpful (e.g., *you drank alcohol*) or unlikely to be helpful (e.g., *you had a warm bath*). These were assessed to determine participants' coping repertoire at baseline, whether the intervention changed their coping strategies, and whether this was related to intervention response. Frequency of use is rated on a 5-category scale (*not at all*, *infrequently*, *moderately frequently*, *very frequently*, *don't know*), and perceived helpfulness on a 5-category scale (*not at all helpful*, *a little helpful*, *moderately helpful*, *very helpful*, *don't know*). Participants are asked to rate a strategy's perceived helpfulness only if they have indicated they had used the strategy (*infrequently *to *very frequently*) in the past month.

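### The plan tests change in self-help behaviour only strategy by strategy over 26 strategies and states no overall between-arm comparison, although the abstract makes behaviour change part of what the trial tests

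*Protocol article*

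**What the plan says.** The Background paragraph of the abstract gives the aim as to "test the efficacy of a low-cost email-based mental health promotion campaign in changing self-help behaviour and preventing more severe depression". The Discussion paragraph of the abstract again pairs better coping behaviour with prevention of depression.

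Under Coping questionnaire: "Participants are asked to rate the frequency and perceived helpfulness of 26 coping strategies for depression symptoms over the past month". This is done twice, once before the first email and once when the six weeks end. Of these, "The coping strategies include the 14 used in the Mood Memos emails" are the promoted ones, and the other 12 were rated by the experts as relatively unhelpful or unlikely to help. The items are collected to learn, among other things, "whether the intervention changed their coping strategies, and whether this was related to intervention response".

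Under Statistical analysis, coping strategies used are listed among the other outcomes, below the primary outcome (PHQ-9) and the secondary outcomes (K10 and Work and Social Adjustment Scale). Usage rates and change in usage are to be compared for each strategy, and then: "Change in use of each strategy will be evaluated using logistic regression expressed as odds ratios with their 95% confidence intervals". Perceived helpfulness of each strategy among its users is also compared between groups, but that concerns opinion of a strategy, not its use. The section states no total score, global test, key strategy, ordering or error control for strategy use.

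**The concern.** Whether the campaign changed self-help behaviour is a single question, and the stated analysis returns 26 answers without saying how to combine them. If the emails change nothing, one or more intervals will often exclude 1 by chance. If they produce a modest rise across the promoted set, most single odds ratios will be non-significant and the result will look patchy. In both cases the answer depends on which odds ratios the reader picks out.

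The article also intends to use coping change to judge whether any change in depression might be due to it. A selective reading of the coping results would carry over into that explanation.

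**Working it through.** **Inputs.** Number of strategies: 26, of which 14 promoted (Coping questionnaire). Error per comparison: 5% two-sided, hence 2.5% in the favourable direction, implied by the 95% interval (Statistical analysis). Correlation between strategies: not given, so a range of 0 to 0.5 is assumed.

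**Step 1: the plan's own figures.** The article gives no error rate for the coping analysis, so only the sample size can be reproduced. With a pre-post correlation of 0.5, the change-score SD is √(2 × (1 − 0.5)) = 1. Then n = 2 × (1.960 + 0.842)² × 1² / 0.2² = 392.4, or 393 per arm, as stated. With 33% dropout, 2 × 393 / 0.67 = 1,173.1, or 1,174, which the target of 1,200 covers. Expected completers are 1,200 × 0.67 / 2 = 402 per arm, so about 400 is used in step 4.

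**Step 2: no effect, independent strategies.**
- At least one of 26 intervals excludes 1, either direction: 1 − 0.95^26 = 0.736. Expected number: 26 × 0.05 = 1.3.
- At least one of the 14 promoted, either direction: 1 − 0.95^14 = 0.512.
- At least one of the 14 promoted, favourable direction only: 1 − 0.975^14 = 0.298.

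**Step 3: no effect, correlated strategies.** Let the test statistics share a common correlation r. The probability is 1 − ∫ φ(x) [Φ((c − x√r)/√(1 − r)) − Φ((−c − x√r)/√(1 − r))]^k dx, with c = 1.96 and k strategies. For the favourable direction the second Φ is dropped.

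| r | any of 26 | any of 14 | favourable among 14 |
|---|---|---|---|
| 0 | 74% | 51% | 30% |
| 0.1 | 72% | 50% | 27% |
| 0.2 | 68% | 48% | 25% |
| 0.3 | 62% | 44% | 22% |
| 0.5 | 48% | 35% | 17% |

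Correlation between the answers themselves translates into weaker correlation between the test statistics. Simulating binary items with 393 per arm gave 74%, 71%, 69% and 62% for any of 26 at latent item correlations of 0, 0.2, 0.3 and 0.5.

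**Step 4: one score against single strategies.** Simulation assumptions (none from the article except the approximate arm size and the 0.5): 400 per arm, 40% baseline use, latent pre-post correlation 0.5, every comparison adjusted for baseline, linear tests standing in for the logistic ones.
- No effect: a sum of the 14 promoted strategies rejects in about 5 to 6% of runs.
- Broad shift, each promoted strategy rising from 40% to 45%: each single test has about 33% power. The sum has 99%, 96% and 90% at between-strategy correlations of 0.1, 0.2 and 0.3.
- Narrow shift, two strategies rising from 40% to 52%: each single test has about 95% power. The sum has about 50%, 27% and 18% at correlations of 0, 0.2 and 0.3.

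Neither analysis replaces the other. The sum answers the overall question under a broad shift, and the single odds ratios are needed for a narrow one.

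**The case against.** Five points can be made in defence of the plan.

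- **Status.** The Aim section says the study "will evaluate the impact of the intervention on depression symptom severity and incidence rates of major depression", and the primary hypothesis is also about depression. Coping is an other outcome, collected largely to explain change in depression. This stands: no primary or secondary conclusion depends on the coping analysis.
- **The decision rule.** The article reports odds ratios with intervals. Nowhere does it say that one interval excluding 1 means behaviour changed. This also stands. A reader might infer that the plan carries a 74% false-positive rate, but the document does not support that. The figure belongs to an assumed rule that also counts falls in use and changes in strategies the emails never promoted. The narrower reading, a favourable result among the 14, gives 30% under independence.
- **Information in the pattern.** It is tempting to say the analysis cannot tell an effective campaign from an ineffective one. That is too strong. In simulations of the broad shift, three or more favourable odds ratios among the 14 appeared in about 70 to 90% of runs, against at most about 3% under no effect. The pattern informs, but no rule for reading it is stated.
- **Uneven effects.** The Active group section tailors wording to familiarity with each strategy and orders strategies by feasibility, so uneven uptake is plausible, and step 4 shows that a sum can miss it. This rules out the score as the only analysis, not as an addition.
- **Unseen documents.** A full protocol or analysis plan may add a summary score or error control. That is possible, and silence on multiplicity alone would be no finding. But this article does fix the single strategy as the unit in which behaviour change is evaluated, and that choice can be assessed as it stands.

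**Conclusion.** The point holds in limited form. The abstract makes behaviour change part of what is tested, while the only analysis stated for change in strategy use is a set of single-strategy odds ratios with no overall comparison and no stated error control.

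If single intervals were used to declare behaviour change, the chance of a false declaration would depend on the reading adopted and on the correlation between strategies. Over test-statistic correlations of 0 to 0.5 it runs from 74% down to 48% for any of 26, 51% to 35% for any of 14, and 30% to 17% for a favourable result among the 14. All are well above 5%. Both the rule and the correlations are assumptions. The power comparison also rests on assumed usage rates and effects and reverses when only two strategies change.

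The change is worth making but does not affect the validity of the main trial result.

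**What to change.** In the Statistical analysis section, add one pre-specified between-arm comparison as the overall test of behaviour change: the number (or summed frequency) of the 14 promoted strategies used at post-intervention, active versus control, adjusted for the same score at baseline. List the 14 questionnaire items that enter the score, since Table 1 shows 12 email topics, and say how a 'don't know' answer is scored.

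Keep the per-strategy odds ratios, either labelled exploratory or with false discovery rate control, so that an effect confined to a few strategies is still seen.

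The cost is a few sentences. All items are already collected at both time points, and no participants are added. The downside is that the score weights strategies equally and has low power if only one or two change, which is why the per-strategy results must stay beside it.

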### Active group

Email messages for the intervention group are based on self-help strategies endorsed by depression experts [10] (see Table 1 for an overview). These self-help strategies were expanded into lengthier email messages. The emails aim to change participant behaviour rather than passively increase knowledge, and as such, their design was informed by theories of behaviour change, persuasion, health communication, and communication on the web [23-32]. Each message contains a brief overview of the strategy, a lengthier explanation of the strategy, why the strategy would work, tips on how the strategy could be implemented, suggested solutions for barriers to implementing the strategy, and an appeal to commit to implementing the strategy. The content of the messages (e.g., strategy rationales, potential barriers and solutions) was derived from professional books, and posts on depression forums by consumers [33-37]. Messages were refined further by a working group of mental health researchers (including consumer researchers). The messages have minimal tailoring to individual participant characteristics [38]. For example, links to internet resources are tailored based on country of residence and the wording advocating each strategy is tailored to the participant's familiarity with using each strategy [29], as indicated during the baseline questionnaire. The strategies are ordered from highest to lowest feasibility to carry out, based on rankings from the original expert study [10]. This is consistent with clinical advice [39,40] to start homework with simple, feasible tasks and build up with time and success.

**Table 1 T1:** Overview of Mood Memos Emails

Order	Active	Control
**1**	Get out of the house	What is depression?

**2**	Fight the desire to do nothing	What types of depression are there?

**3**	Set yourself a small goal and reward yourself for reaching it	Can depression cause physical health problems?

**4**	Eat well	Depression and other mental health problems

**5**	Improve your sleep habits	What is the history of depression?

**6**	Do something you enjoy and that gives you a sense of achievement	What causes depression?

**7**	Talk to someone supportive about your problems and how you feel	Who is at risk of depression?

**8**	Get active	How common is depression?

**9**	Do what has worked for you in the past	Burden of depression

**10**	Let others know how you are feeling	Is depression a weakness?

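### The logistic regression for change in coping use has no stated response; if it is yes/no, as the text most naturally reads, it discards much of a four-level frequency that is already collected

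*Protocol article*

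**What the plan says.** The Coping questionnaire section covers 26 strategies: "Participants are asked to rate the frequency and perceived helpfulness of 26 coping strategies for depression symptoms over the past month", at baseline and post-intervention. "Frequency of use is rated on a 5-category scale": four ordered levels (*not at all*, *infrequently*, *moderately frequently*, *very frequently*) plus *don't know*.

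That section also holds the article's only definition of having used a strategy, as a routing rule: "Participants are asked to rate a strategy's perceived helpfulness only if they have indicated they had used the strategy", with use meaning *infrequently* or more.

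The Statistical analysis section lists coping under other outcomes and gives the purpose of evaluating it in a sentence that begins: "In order to determine whether any change in depression might be due to changes in coping behaviour, the coping strategies used by participants will be". It continues: "Usage rates and change in usage of each strategy in each intervention group will be compared pre- and post-intervention". Then comes the method: "Change in use of each strategy will be evaluated using logistic regression expressed as odds ratios with their 95% confidence intervals". The next sentence compares mean perceived helpfulness among those using each strategy.

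The article does not say whether the model is binary or ordinal, where any cut lies, or how baseline use and *don't know* enter.

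**The concern.** Logistic regression without qualification usually means a binary response, and the talk of usage rates points the same way. The helpfulness comparison strengthens this. Only people reporting *infrequently* or more give a helpfulness rating, so using a strategy must mean any use there, one sentence after the regression is described.

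On that reading, a participant who moves from *infrequently* to *very frequently* is a user both times and shows no change, while a move from *not at all* to *infrequently* counts in full. The active emails are also written for people who already use a strategy, since "the wording advocating each strategy is tailored to the participant's familiarity with using each strategy". Among existing users, the effect sought is more frequent use, which any-use coding cannot see.

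The abstract states the aim as testing efficacy "in changing self-help behaviour and preventing more severe depression in adults with sub-threshold depression", and the coping analysis is meant to show whether change in depression could come from change in coping. An insensitive response could suggest that behaviour did not change when it did.

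**Working it through.** **The plan's own figure.** The article gives no figure for the coping analysis. Its sample size, for a continuous outcome, reproduces: 2 × (1.960 + 0.842)² / 0.2² = 392.4, so 393 per condition (two-sided 5% assumed). With a pre–post correlation of 0.5, the change-score variance factor 2(1 − 0.5) is 1, so change scores also give 393. I use 393 per arm below only as a convenient analysed number.

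**Which moves register.** Code the levels 0 to 3. There are six upward moves: 0→1, 0→2, 0→3, 1→2, 1→3, 2→3.
- Any use (cut at 1): 1→2, 1→3 and 2→3 are lost, 3 of 6.
- *Moderately frequently* or more (cut at 2): 0→1 and 2→3 are lost, 2 of 6; 1→3 registers.
- An increased-use indicator registers all six, but a one-step rise counts the same as a three-step rise.

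These counts are not weighted by how likely each move is.

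**Illustrative power.** Assumptions, none from the documents: common odds ratio 1.5, two-sided 5%, post-intervention comparison without baseline adjustment, and five control-arm distributions over levels 0 to 3. The active-arm distribution follows by multiplying each cumulative odds by 1.5. Let p_i be the level proportions averaged over arms and u the averaged proportion at or above a cut. Then:
- ordinal information = n(1 − Σp_i³)/6
- binary information = n·u(1 − u)/2
- power = Φ(ln 1.5 × √information − 1.96)

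First scenario, controls (0.05, 0.25, 0.40, 0.30): odds of any use are 0.95/0.05 = 19 in controls and 28.5 in the active arm, so 0.9661 use the strategy there and u = 0.95805. Binary information = 393 × 0.95805 × 0.04195 / 2 = 7.90. Averaged proportions are (0.0419, 0.2192, 0.3932, 0.3457), Σp_i³ = 0.1127, and ordinal information = 393 × 0.8873 / 6 = 58.12. Ratio = 7.90/58.12 = 14%. Any-use power = Φ(0.4055 × 2.811 − 1.96) = Φ(−0.82) = 21%. Ordinal power = Φ(0.4055 × 7.624 − 1.96) = Φ(1.13) = 87%.

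| Control distribution (levels 0–3) | Ordinal power | Any-use power | Information kept, any use | Information kept, cut at 2 | Information kept, best single cut |
|---|---|---|---|---|---|
| .05, .25, .40, .30 | 87% | 21% | 14% | 65% | 76% (cut at 3) |
| .10, .30, .35, .25 | 88% | 35% | 25% | 75% | 75% (cut at 2) |
| .20, .35, .30, .15 | 88% | 57% | 46% | 81% | 81% (cut at 2) |
| .30, .35, .25, .10 | 88% | 70% | 63% | 78% | 78% (cut at 2) |
| .50, .25, .15, .10 | 87% | 81% | 84% | 70% | 84% (cut at 1) |

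The best cut differs between scenarios, so no one cut chosen in advance suits all strategies, and even the best keeps only 75–84%.

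**The case against.** The strongest objection is that the article never says the regression is on used versus not used. A reader might infer this as the stated plan, but it takes two separate texts to get there, and the definition of use is written as a routing rule for the helpfulness question. A cut at *moderately frequently*, an increased-use indicator or a proportional-odds model would all fit the sentence, and each would register *infrequently* to *very frequently*. This stands: any-use coding is the natural reading, not a documented choice. A condensed article may also leave response coding to a fuller document, so the silence alone is no fault.

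A reader might also infer that most participants already use the promoted strategies, so that any-use coding sits near its ceiling. The documents give no usage rates. Participants have symptoms that affect their functioning, and Table 1 includes less everyday items such as relaxation techniques and setting a small goal with a reward. With 50% use among controls the loss is modest (81% against 87%).

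Finally, coping is neither a primary nor a secondary outcome, and the sample size was not set for it. This also stands and limits the weight of the point. None of it removes the case for an ordinal model, which is better than any single cut in every scenario above.

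**Conclusion.** The point holds as a modest improvement, not as an error in a main analysis. The article collects an ordered frequency at two time points and names a method that most naturally reduces it to yes/no. If the coding is any use, half the possible upward moves do not register, and the illustrated power per strategy is 21–81% against 87–88% for an ordinal model. If another single cut is meant, the loss is smaller but remains.

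The power and information figures rest on an assumed odds ratio of 1.5, 393 analysed per arm, assumed distributions and proportional odds. They show how far the loss can range, not what it will be in this trial. The conclusions on PHQ-9, K10 and WSAS are unaffected.

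**What to change.** In the Statistical analysis section, state that each strategy's post-intervention frequency, on its four ordered levels, will be analysed by proportional-odds logistic regression on group, adjusted for that strategy's baseline frequency, with *don't know* treated as missing. Report the odds ratio with its 95% confidence interval, as already promised, and keep any-use rates by group and time as description.

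The cost is a change of wording; no new data are needed. The proportional-odds assumption must be checked for each strategy. Name the fallback in advance: binary logistic regression with the cut at *moderately frequently* or more, which keeps 65–81% of the ordinal information in the scenarios above.
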